#### Assessments

All patients enrolled in the study will participate in three face-to-face visits and two phone calls. The initial visit, 6-month visit, and 12-month visit will use instruments to measure functional status, quality of life, cognition, mood, self-reported outcomes, attitudes, behaviors, and compliance. At the initial visit, the patient's Mayo current visit information and family history will be collected. At 3 months and 9 months, the study team will call the patient for descriptions of quality of life and mood. If the results indicate a risk to the patient, the patient's primary care physician will be contacted. Specifically, if the patient health questionnaire PHQ-9 indicates depression (score >14)[5], or the Kokmen Short Test of Mental Status indicates memory loss or changes of functional status (≤29)[6], this finding will be reported to the primary care physician.

The instruments used in this study measure quality of life, mood, functional status, activities of daily living, caregiver burden, and self-reported outcomes of hospitalization and ED visits. The SF-12, the short form of the SF-36, which measures quality of life and psychosocial factors[7], will determine if the quality of life has changed due to the intervention. The PHQ-9 is a validated instrument that measures depression using Diagnostic and Statistical Manual (DSM) 4 criteria for depression[5] and a scoring mechanism that can measure depressive symptoms over time. The Kokmen Short Test of Mental Status screens for cognitive decline using a 38-point screening instrument[6]. The functional measures include grip strength with tonometry, which can directly measure a person's strength in the upper extremities[8]. Both upper extremities will be tested and the best result used as the primary measure. The timed up-and-go test is a validated instrument that measures the ability to rise from a chair, turn, and return to the chair[9]. Lastly, gait speed is measured in meters per second. The patient is told to walk as quickly as possible for 6 meters. Standards for gait speed are established for older adults[10]. The Barthel Index is a self-reported questionnaire that evaluates activities of daily living for the subject[11]. The Caregiver Quality of Life Scale is used as the standard instrument for measuring caregiver stress and feelings. Outcomes include hospital admissions and visits to the ED within the past 3 months. The healthcare providers are surveyed once in the pre-stages of the study and once after completion. Providers are asked these questions:

• How confident are you in the home monitoring of your sickest patient?

• Do you feel that our practice has a good system of maintaining the functional status and health of our patients?

• How confident are you that a home-based system that allows monitoring of vital signs and symptoms will help in patient care?

• Would you be willing to recommend a home-based telemonitoring system that allows videoconferencing?

#### Outcomes measurement

The primary outcomes are hospitalizations, ED visits, and the composite outcome of hospitalizations and ED visits. Olmsted County has two primary medical centers, and all listed outcomes can be collected through the Rochester Epidemiology Project. Patient self-reports will also be used to capture care provided outside of Olmsted County, and these events will be verified by the study team. In addition, Medicare claims data will be reviewed for hospitalizations and associated costs. In practical terms, almost all patients who visit PCIM preferentially use Mayo facilities for ED and hospital care. These measures will be obtained from the medical record.

An economic analysis will be performed comparing usual care and home telemonitoring, including total non-elective care costs based on reimbursement from Medicare, Medicaid, and private insurance. Cost analysis will also use standard Centers for Medicare and Medicaid Services (CMS) costing information and reimbursement information. This will include inpatient, outpatient, and skilled nursing facility stays, and home healthcare adjusted for CMS Hierarchical Condition Codes and regional variation as well as all direct and indirect costs of the telemonitoring.

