Home telemonitoring may reduce hospital admissions, emergency department (ED) visits, and hospital length of stay[2]. A systematic review suggests a 20% reduction in hospitalization in home telemonitoring groups compared with the usual care in patients with cardiovascular disease[3]. However, it remains unclear if home telemonitoring will reduce hospitalizations and ED visits in older patients with multiple medical problems. We propose to answer this question in a sample of high-risk adults at least 60 years of age with mixed chronic diseases in a randomized controlled trial. Our primary aim is to evaluate the effectiveness of home telemonitoring for reducing hospitalizations, emergency department visits, and the composite outcomes of hospitalizations and ED visits compared with usual care. Our secondary aims are to evaluate the effectiveness of home telemonitoring for improving functional status, quality of life, patient attitudes, behaviors, compliance, mood, and cognitive status compared with usual care. Furthermore, we intend to evaluate the effectiveness of home telemonitoring for decreasing total healthcare costs, 30-day re-hospitalization rates, and hospital bed days.

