### Demographic and practice information

Most residents of Olmsted County who are age 60 or older are female and white (>90%)[4]. While county residents are largely Northern European, the ERA index places this ethnicity as a high-risk population; thus, the potential sample may slightly over represent underserved minorities as a high-risk group.

The PCIM and FM have a combined population of about 21, 000 patients in this age group. The selection criteria of a score of 16 or greater on the ERA places these individuals in the upper decile of risk for hospitalizations, ED visits, nursing home placement, and death. The ERA is an electronically derived index number provided to all patients in the in PCIM and FM via the GDMS (Table 1).

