The system provides alerts and feedback if there is a worrisome response to a question or if vital signs are outside of preset limits. The RN communicates with the patient and seeks assistance from the subject's primary care provider or the overseeing NP for management issues. The NP or RN communicates with the patient via teleconferencing to facilitate appropriate actions, which may include limited advice, reset thresholds, timely provider outpatient visit, or ED evaluation. The use of qualified staff allows for diagnostic and treatment decisions for a wide variety of complex medical conditions that may not be amenable to protocol-based care. The participants are told to call 911 for emergencies because the Intel Health Guide is not a life-saving device.

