### Data analysis

All analysis will be performed according to group using an intention-to-treat method. The primary outcomes of combined hospitalizations and ED visits will be analyzed using a time-to-event, Cox proportional analysis. Adjustment will be made to the time-to-event analysis only if there are clear differences between the randomized groups. As a secondary method of analysis, the total number of ED visits and hospitalizations will be compared using a t-test. Initial descriptive data will be presented with means and standard deviations for parametric data. Non-parametric data will be presented with modes and 25 to 75 interquartile ranges.

Secondary data analysis will involve comparisons between the intervention group and the usual care group, with these dependent variables: SF-12 scores and sub scores, PHQ-9 scores, Kokmen Short Test of Mental Status scores, Katz Index of Independence in Activities of Daily Living scores, and Likert Scale scores for attitudes toward health and compliance (Table 4). All categorical variables will be analyzed using a t-test where appropriate, and proportional variables will be analyzed using chi square analysis for secondary outcomes. All tests for significance will use an alpha *p*-value of 0.05. Adjustments for multiple comparisons will be used for secondary analysis. All tests will assume a two-sided *p*-value.

**Table 4 T4:** Statistical analysis for secondary outcomes

Instrument/measure	Variable type	Test	Significance
**Kokmen Short Test of Mental Status**	Continuous score	t-test	Alpha 0.05

**SF-12**	Proportional for items or continuous	Fisher's exact test or t-test	Alpha 0.05

**Likert scale scores for attitudes and behavior**	Continuous	t-test	Alpha 0.05

**PHQ-9**	Continuous	t-test	Alpha 0.05

**Katz Index of Independence in Activities of Daily Living**	Continuous	t-test	Alpha 0.05

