Telemonitoring using updated equipment has been quite successful for chronic disease management. The initial use of telemonitoring targeted patients who live long distances from medical or specialty care[15]. Increasingly, telemonitoring has sought to help individuals with chronic illnesses (e.g., CHF, chronic obstructive pulmonary disease [COPD], diabetes) that require daily or frequent monitoring. The goal of telemonitoring is to identify and treat symptoms, functional decline, and other key changes in medical status before the patient requires acute care in an ED or hospital or long-term care in a skilled nursing facility. The results of many demonstration projects and pilot studies evaluating the effectiveness of telemonitoring have been favorable; however, the projects have been often limited to a single disease model. Diabetes has been widely studied in randomized controlled trials[16-18]. In the diabetic population, using a meta-analysis, on aggregate, the patients favorably endorsed home telemonitoring and had lower hospital readmissions and improved hemoglobin A1c levels[3]. In the CHF studies, all-cause mortality dropped by 40% and hospitalizations by 20%[3]. Some of the CHF studies did not demonstrate a decrease in ED visits compared with usual care[19].

Patients with mixed chronic diseases remain the most understudied group, yet many older adults have more than one chronic illness[20]. In a randomized controlled trial of 53 patients with CHF, COPD, or a chronic wound, fewer patients were re-hospitalized in the telemonitoring group, which used a device capable of videoconferencing and physiologic monitoring of vital signs, spirometry, and pulse oximetry[21]. In a similar study of 104 patients with CHF, COPD, and/or diabetes, Noel[22] demonstrated reduced bed days and ED visits when patients at home used a device capable of measuring vital signs, blood glucose levels, three-lead electrocardiography, pulse oximetry, auscultation of heart and lungs, and pain assessment. However, cost analysis was limited to a previous 6-month comparison, making interpretation difficult. Videoconferencing was not available for this study. In a recent review for the Canadian government, this study was the only publication on elderly patients with mixed chronic disease given the quality score of B (good), with the remainder deemed to have significant shortcomings[3].

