The primary concern for many healthcare organizations undertaking telemonitoring is the cost justification for the clinical and capital investment. While the cost benefits of reduced utilization and functional decline are self-evident, the costs of telemonitoring have not been well-analyzed to date. In an example analysis of a single published work, the estimated annual cost for patients in the telemonitoring group was $14,678, compared with $10,161 for the usual care[3]. However, remaining methodologic issues suggested lack of comprehensive cost accounting and validated staffing protocols. Moreover, the quality of the economic evaluations to date have been deemed poor, and the report called for more studies of higher methodologic quality to include more diverse patient populations with CHF, diabetes, and COPD to increase external validity[3].

The proposed study will address the need for more rigorous study of the role of home telemonitoring in elderly patients with mixed chronic disease. We will use a unique, validated risk assessment index to systematically identify patients at high risk for hospitalization, ED visits, nursing home placement, and death. The study size will exceed the largest study to date for the mixed chronic disease population. We will provide a more robust analysis of key clinical outcomes and economic impacts not yet fully characterized and use these results in future studies comparing telemonitoring to care-transition programs. We will also use the results to define populations most suitable for these and similar interventions targeted to sustaining late-life independent living. This study may also provide a background for other monitoring devices.

The strengths of this study include the randomized trial approach, which will allow the groups to be randomly assigned and minimize the differences between the groups. The usual care group includes the standardized followup for patients, which is the standard of care for high-risk elderly patients in Rochester. The telemonitoring intervention group is based on cutting-edge technology for monitoring at home. The clinical group includes experienced midlevel nurse providers and RNs who oversee the management of home medical care. Patients also have a connection with their primary physician, who is informed of major clinical changes. Lastly, the group is maintained in a closed medical system of two major hospital groups in Olmsted County, with most care provided by the PCIM.

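### Patients are selected for high risk of death, yet death is in no listed outcome, so a mortality difference between arms would go unseen and could flatter or dilute the result

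*Protocol article*

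**What the plan says.** On who is enrolled, Demographic and practice information says that the score cut-off "places these individuals in the upper decile of risk for hospitalizations, ED visits, nursing home placement, and death". The Discussion repeats that the index serves to "systematically identify patients at high risk for hospitalization, ED visits, nursing home placement, and death".

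On what is measured, Outcomes measurement states: "The primary outcomes are hospitalizations, ED visits, and the composite outcome of hospitalizations and ED visits". The clinical secondary aims in Background are "improving functional status, quality of life, patient attitudes, behaviors, compliance, mood, and cognitive status compared with usual care", followed by costs, 30-day readmission and bed days. Data analysis and Table 4 add SF-12, PHQ-9, Kokmen, Katz and Likert scores.

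On analysis, Data analysis says: "The primary outcomes of combined hospitalizations and ED visits will be analyzed using a time-to-event, Cox proportional analysis". As a secondary method, "the total number of ED visits and hospitalizations will be compared using a t-test". No rule for a patient who dies is given, and the Sample size section assumes no dropout.

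Mortality as something telemonitoring may affect appears once, in the Discussion's review of other studies: "In the CHF studies, all-cause mortality dropped by 40% and hospitalizations by 20" percent.

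**The concern.** The index is presented as predicting four things. Two of them are the primary outcomes. Death, the gravest of the four, is compared between arms nowhere in the article.

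This matters more here than in many utilization trials, because unblinded staff in one arm help decide whether part of the endpoint occurs. Under Intervention - home telemonitoring, an alert leads to actions "which may include limited advice, reset thresholds, timely provider outpatient visit, or ED evaluation". Fewer ED visits could mean that deterioration was prevented, or that some of it was not reached in time. Deaths by arm are the most direct check between these explanations.

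There is also a technical side. With the endpoint as defined, a death before a first admission or ED visit contributes no event, and a patient who dies early has less time in which to be counted in the t-test on totals. A mortality difference in either direction can therefore leak into the utilization result without being shown.

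**Working it through.** **1. Where death appears.**

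| Place in the article | Content | Death? |
|---|---|---|
| Background, primary aim | hospitalization, ED visits, composite | no |
| Background, secondary aims | function, quality of life, attitudes, behaviors, compliance, mood, cognition; costs, readmission, bed days | no |
| Outcomes measurement | primary outcomes; economic analysis | no |
| Data analysis, Table 4 | five instruments or scales | no |
| Demographic and practice information; Discussion | risks the index selects for | yes, as a risk only |
| Discussion | results of CHF studies | yes, as background only |

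**2. The plan's own figure.** No stated figure involves death. The sample size does reproduce closely. Reading 0.380 and 0.285 as event-free proportions, HR = ln(0.380)/ln(0.285) = 0.771. Schoenfeld's formula gives 4 × (1.960 + 0.842)² / (ln 0.771)² = 465 events, against the stated 463. Freedman's formula gives 470 events and 470/(0.620 + 0.715) = 352 per group, as stated. Nothing in it allows for deaths.

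**3. How far deaths could move the planned analyses.** This was simulated with 400,000 patients per arm and no true effect on admissions or ED visits.

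- One-year first-event risk, equal in both arms: 38.2% (the yearly rate in the Sample size text) or 59.8% (the usual-care rate implied by the first row of Table 3: 38.2/(1 − 0.361)).
- One-year mortality, assumed because the article gives none: 5% under usual care; 5, 10, 15 or 20% under telemonitoring.
- Link between death and admission: a gamma frailty with mean 1 and variance θ = 0 (independent), 1 or 2, multiplying both hazards. The one-year cumulative hazard for a risk p is [(1 − p)^(−θ) − 1]/θ, or −ln(1 − p) when θ = 0.
- Visit counts: Poisson over the time alive, up to one year.

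With 5% mortality in both arms every ratio lay between 0.995 and 1.004, as it should. Ratios of telemonitoring to usual care with 10 to 20% mortality under telemonitoring:

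| Analysis | Independent | Shared frailty |
|---|---|---|
| Cox HR, censored at death | 0.99–1.00 | 0.92–0.99 |
| Cox HR, dead kept at risk to 12 months | 0.91–0.98 | 0.86–0.97 |
| Ratio of mean counts (the t-test) | 0.92–0.98 | 0.77–0.95 |
| Cox HR, death added to the composite | 1.06–1.32 | 1.01–1.22 |

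One scenario as an example (risk 38.2%, θ = 1, mortality 5% against 15%): 0.97 censored, 0.92 kept at risk, 0.90 for counts, and 1.15 with death in the composite.

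For scale, a fall from 59.8% to 38.2% corresponds to a hazard ratio of ln(0.618)/ln(0.402) = 0.53. A shift to 0.92 is small beside that.

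**4. The other direction.** Swapping the arm labels inverts the ratios. If usual care had 10 to 20% mortality and telemonitoring 5%, the censored Cox HR under shared frailty would be 1/0.99 to 1/0.92 = 1.01 to 1.09, and the count ratio 1/0.98 to 1/0.77 = 1.02 to 1.30. A real benefit would be diluted.

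**The case against.** - **No rule for death is stated.** This stands. A censoring rule is commonly left to the analysis plan, and its absence is no finding. A reader might infer that the primary analysis treats the dead as event-free survivors; the article does not say so. Censoring removes them from the risk set, and only keeping them at risk to 12 months would treat them that way.
- **Excess deaths need not look like benefit.** This also stands. If death is independent of admission risk, censoring leaves the Cox hazard ratio at about 1.00. A reader might compute a larger distortion by letting k of 100 deaths each replace an admission at the same moment: (59.8 − k)/59.8 = 0.97, 0.92 and 0.83 for k = 2, 5 and 10. That needs one-for-one replacement in one arm only, which nothing in the article supports as the expected case.
- **The only mortality evidence cited is a reduction.** True. It means the bias may equally run against telemonitoring, which is a further reason to look.
- **ED evaluation is among the permitted responses to an alert, and patients are told to call 911 in emergencies.** True. The article does not support reading the intervention as keeping patients from the ED. The point is only that staff can influence whether a visit occurs.
- **Table 4 is not a complete list, and the article condenses a fuller protocol.** Costs, bed days, gait speed and grip strength are planned but not in Table 4, so absence there alone proves little. The full protocol may record deaths. But the article sets out its aims and outcomes in Background, Outcomes measurement and Data analysis, and death is missing from all three. Which outcomes a trial has is not a detail normally left to the analysis plan.

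**Conclusion.** The point holds in a limited form. The article selects for risk of death and lists no comparison of it, so a mortality difference would not be visible in the listed results. That follows from the text and needs no assumption.

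The numerical effect is conditional. It rests on an assumed 5% against 10 to 20% mortality, no true effect on admissions, and, for the censored Cox model, shared frailty. That last assumption is plausible, since one index is said to predict both outcomes. In these scenarios the censored Cox model moves by at most about 8%, a Cox model that keeps the dead at risk by up to 14%, and the count comparison by up to 23%. The count comparison and the kept-at-risk model shift even when death is independent of admission risk. Smaller mortality differences give smaller shifts.

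This is a worthwhile and inexpensive improvement to the outcome set. It is not evidence that the primary result will be wrong, nor that telemonitoring is expected to raise mortality.

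**What to change.** 1. In Background and Outcomes measurement, list all-cause death within 12 months by randomized arm as a safety outcome. Report it descriptively, with a confidence interval, next to the primary result.
2. In Data analysis, add a prespecified supportive Cox analysis of time to first hospitalization, ED visit or death.
3. In Data analysis, replace the t-test on raw totals with a comparison of event rates that accounts for time alive.

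Use these to interpret the primary result, not as a condition for claiming benefit. With 100 per arm and equal true mortality, telemonitoring shows more deaths by chance with probability (1 − P(tie))/2. The chance of a tie is about 13% at 5% mortality and 8% at 15%, so this is about 43 to 46%. A rule requiring no excess would block a true benefit nearly half the time.

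The cost is wording, one extra model and one table. The medical record, the Rochester Epidemiology Project and Medicare claims are already named as sources under Outcomes measurement; that they capture deaths should be confirmed. The mortality estimate will be imprecise: at 5% against 10%, the 95% interval for the difference is about ±1.96 × √(0.05 × 0.95/100 + 0.10 × 0.90/100) = ±7.3 percentage points.

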## Abstract

**Background:**

Older adults with multiple chronic illnesses are at risk for worsening functional and medical status and hospitalization. Home telemonitoring may help slow this decline. This protocol of a randomized controlled trial was designed to help determine the impact of home telemonitoring on hospitalization. The specific aim of the study reads as follows: to determine the effectiveness of home telemonitoring compared with usual care in reducing the combined outcomes of hospitalization and emergency department visits in an at-risk population 60 years of age or older.

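### The protocol names one primary outcome in some places and three in others, and it states no error control if all three are primary

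*Protocol article*

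**What the plan says.** Two places list three primary outcomes:

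- Outcomes measurement: "The primary outcomes are hospitalizations, ED visits, and the composite outcome of hospitalizations and ED visits".
- Background, primary aim: to evaluate telemonitoring "for reducing hospitalizations, emergency department visits, and the composite outcomes of hospitalizations and ED visits compared with usual care".

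Neither gives an order, a gatekeeping step or a rule for how many must succeed.

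Three places point to the composite alone:

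- Abstract, specific aim: effectiveness "in reducing the combined outcomes of hospitalization and emergency department visits in an at-risk population 60 years of age or older".
- Data analysis: the only primary test named is a Cox time-to-event analysis of the two event types taken together.
- Sample size: the prose statement for the actual 100 per group is a detectable 36.1% fall in the combined outcome.

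The abstract's Methods/Design paragraph uses the plural for the primary outcomes and does not say whether they are combined.

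On error control, Data analysis says "All tests for significance will use an alpha *p*-value of 0.05" and "Adjustments for multiple comparisons will be used for secondary analysis". Nothing is said about adjustment among primary outcomes.

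**The concern.** The number of primary outcomes decides what the headline result means. Suppose hospitalization reaches p<0.05 and the composite does not. Under the abstract the trial has missed its aim. Under Outcomes measurement it has a significant primary outcome. The protocol supports both accounts, so the choice could be made after the results are known.

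This is not a detail left to an analysis plan that is not shown. The document answers the question, in conflicting ways. It also addresses multiplicity and assigns it only to secondary analysis, so a three-outcome primary claim would carry no stated protection.

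**Working it through.** **1. The plan's own figures.** The Sample size section gives 352 per group and 463 events for 0.380 versus 0.285 at two-sided 0.05 and 80% power.

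- Hazard ratio = ln(0.380)/ln(0.285) = (−0.968)/(−1.255) = 0.771, as stated.
- Events (Schoenfeld) = 4(1.960 + 0.842)²/(ln 0.771)² = 31.4/0.0676, about 464.
- Per group, from Freedman's 469 events: 469/(2 − 0.380 − 0.285) = 351.3, so 352.

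Table 3 follows from a two-proportion formula with continuity correction at 0.05 and 80% power:

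- Hospitalization column: 100, 150, 201, 249, 300 and 352 for the stated 100 to 350.
- Composite column: 93 for the row of 100, then 149, 200, 250, 300 and 354.

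So hospitalization and the composite are each sized at a full, unsplit 0.05. ED visits alone are not sized. No familywise error rate is stated anywhere.

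**2. Control rates, back-calculated from Table 3.**

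- Hospitalization: 27.1/(1 − 0.425) = 47.1%.
- Composite, row of 100: 38.2/(1 − 0.361) = 59.8%.
- Composite, other rows, for example 44.4/(1 − 0.246) = 58.9%.

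The Sample size prose calls 38.2% the yearly rate, whereas Table 3 puts it in the intervention column. Only the Table 3 reading fits here, because a composite rate cannot be below the 47.1% for one of its components.

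**3. Overlap, an assumption.** The protocol gives neither an ED-visit rate nor the share of admissions that come through the ED. That share, f, was varied from 0 to 95%.

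With exponential times over one year:

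- Hospitalization hazard: −ln(1 − 0.471) = 0.637.
- Composite hazard: −ln(1 − 0.589) = 0.889.
- Hazard of ED visits without admission: 0.889 − 0.637 = 0.252.
- ED hazard: 0.637f + 0.252. At f = 0.5 this is 0.571, a one-year ED rate of 43.5%.

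**4. Error rate if any one of three counts.** Log-rank tests were simulated with no treatment effect: 100 per arm, one year, 40,000 trials per setting (Monte Carlo standard error about 0.15 percentage points). Ranges cover composite control rates of 58.9% and 59.8%.

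| Admissions through the ED | Implied one-year ED rate | At least one of three p<0.05 | At least one favouring telemonitoring |
|---|---|---|---|
| 0% | 22.3–24.0% | 11.7–12.0% | 6.0% |
| 25% | 33.7–35.2% | 11.4% | 5.6–5.8% |
| 50% | 43.5–44.7% | 10.7% | 5.3% |
| 75% | 51.8–52.8% | 9.9–10.1% | 4.9–5.1% |
| 95% | 57.6–58.5% | 8.5–8.9% | 4.3–4.6% |

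Each test taken singly rejected in 4.7–5.2% of trials, so the excess comes from having three chances. The Bonferroni bound is 3 × 0.05 = 15%. Independence would give 1 − 0.95³ = 14.3%, which is only a reference because the composite contains the other two outcomes. Runs with added between-patient heterogeneity and other event rates gave 7.9–12.2%.

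**5. Error rate if the composite alone is primary.** There is one test at two-sided 0.05: 5%, or 2.5% in favour of telemonitoring.

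**The case against.** The strongest reply is that the protocol never sets out three primary tests. The one primary test it names is for the combined outcome, and the abstract's aim and the 100-per-group power statement agree. On that reading the error is 5% and the lists of three are loose wording. This stands in part: inflation is not established as a feature of the plan. It does not remove the point. Two sections call all three primary, Table 3 sizes hospitalization at a full 0.05, and the 0.05 rule covers all tests.

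A reader might infer that the false-positive rate simply is 9–11%. The documents do not support that as fact. It needs all three to be tested as primaries and any one to count as success, and no success rule is written. It also needs an assumed overlap, and the range across plausible overlaps is wider. The figure counts both directions, so the rate of false claims for telemonitoring is about half of it.

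A reader might also infer that Table 4 contradicts the promised secondary adjustment by listing 0.05 for every instrument, and compute 1 − 0.95⁵ = 22.6% for five instruments. That fails. Adjusted p-values are compared with 0.05, and a familywise level can itself be 0.05. The 22.6% describes an unadjusted plan, which the protocol does not have. The choice of adjustment method may properly sit in the analysis plan.

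**Conclusion.** The inconsistency is in the text and needs correction: the protocol has one primary outcome or three depending on the section, and its multiplicity rule leaves out the primaries. The size is conditional. With the composite as sole primary outcome, the two-sided error is 5%. With three primaries and success on any one, it is about 8.5–12%, and no more than 15%. For false claims favouring telemonitoring it is about 4.3–6% against 2.5%.

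These figures rest on the Table 3 control rates, on 0–95% of admissions coming through the ED, and on a success rule that the protocol permits but does not state. No overlap examined brought the three-outcome rate back to 5%. Nothing in this point shows a fault in Table 4 or in the secondary outcomes.

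**What to change.** In the Background aim, Outcomes measurement and Data analysis, name time to first hospitalization or ED visit as the single primary outcome, tested at two-sided 0.05. Align the plural in the abstract's Methods/Design paragraph. Make hospitalization and ED visits secondary in one of two ways: include them in the multiplicity adjustment already promised for secondary analysis, or test them in a prespecified order only if the composite is significant. Table 4 needs no change for this.

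The change is one of wording. It matches the abstract's aim, the Cox analysis and the combined-outcome power statement, and sample size stays as planned. The cost is that neither component can be claimed as a primary success on its own.

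Keeping three primaries under a Bonferroni split (0.0167 each) is also valid, but it costs power. At 100 per arm, by the two-proportion formula without continuity correction, power falls from 87% to 75% for the composite (59.8% versus 38.2%) and from 84% to 71% for hospitalization (47.1% versus 27.1%). The simulated familywise error is then 3.1–4.4%. If that route is preferred, the split and the reduced power should be stated.
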